Many of the tasks of daily life involve DTs, which are a matter of concern given that because of ageing, older people have problems performing the daily live activities simultaneously. The ability to perform any task may be impaired due to limited attentional resources [15], increased risk of falls [16], loss of independence, and impaired quality of life. Previous studies analysing the effect of DT in older women with fibromyalgia found that gait pattern is affected when an additional cognitive task is added to the primary motor activity; so the walking pattern may be safer and more stable if attention is focused on two simultaneous tasks [17,18]. However, no studies have investigated the impact of DT-based exercise programs on cognitive activity and executive function.

Square stepping exercise (SSE) is a type of physical exercise used in the elderly to reduce the risk of falls [19], but its effects on executive function and regucalcin levels have not been examined. Therefore, this study will analyse the effects of SSE on regucalcin, executive function, physical fitness, balance, fall risk, fear of falling, and body composition in older people. In addition, it will assess the relationship between changes in executive function and regucalcin, physical fitness, balance, fall risk, fear of falling, and body composition in older people.

We hypothesized that (1) SSE will enhance regucalcin levels, executive function, physical fitness, balance, fall risk, fear of falling, and body composition in older people, and (2) changes in executive function and regucalcin will be related to falls, body composition, and physical fitness in older people.

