### 2.8. Statistics

Descriptive statistics and computations will be performed through SPSS (version 25.0; IBM SPSS Inc., Armonk, IL, USA). Data will be presented as means and standard deviation (SD).

Normality and homogeneity of data will be checked applying Kolmogorov–Smirnov and Levene’s tests, respectively. Moreover, an intention-to-treat and a per-protocol analyses will be executed:

**Intention-to-treat analysis**. This analysis will consider all randomly assigned participants in their respective group. Missing data will be input by multiple imputations. Repeated measures ANOVA will be applied to calculate the intervention effects on the different dependent variables, adjusted by age and baseline outcomes. Cohen’s d will be included in results (95% confidence interval) as the effect size. Statistical significance will be computed for the effect of time and the interaction group × time. Alpha level shall be set at *p* ≤ 0.05. Pearson’s bivariate correlations and linear regression will be also computed for analysing the associations between variables.

**Analysis by protocol**. For this analysis, only the volunteers who have completed more than 80% of training sessions will be considered. The same procedures as those indicated for intention-to-treat analysis will be conducted.

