## 3. Discussion

Internationally, there are more than 300 publications on SSE in high-impact journals, but none have addressed the aspects that this project aims to study. There are many published studies on physical exercise in older people; however, there is no publication that studies the benefits of SSE on executive function, regucalcin, as well as studying the correlations of these changes with the variables of fall prevention, physical condition, and body composition in older people.

The implementation of the SSE has been investigated in adult populations [42,43], as well as in other populations with pathologies such as diabetes mellitus type 2 [44], Parkinson’s [45], and fibromyalgia [23], among others. Therefore, we hypothesize that a 6-month intervention based on SSE will improve the regucalcin levels, executive function, physical fitness, balance, fall risk, fear of falling, and body composition in older people over 65 years old. Furthermore, if the efficacy of this training system is demonstrated as an improvement in the regucalcin levels, it could reduce the risk of developing cancerous tissues, as well as being used as a biomarker in “active” ageing. Similarly, if there are encouraging results in cognitive performance and balance tests, it could indicate an improvement in functionality and performance in activities of daily living. These improvements will provide older people with independence from external aids that will be needed in the after-effects of ageing. Therefore, the implementation of SSE program could be applied by several agents interested in taking advantage of the benefits of this activity.

The SSE training method stands out because it requires neither expensive material nor any specific installation (it can be carried out in open and enclosed spaces) and reports a high applicability due to its adherence and feasibility [46]. Thus, it is a low-cost system standardized by different levels of difficulty (see methodology) that can be implemented at low cost in the public and private health sectors. Therefore, within the public health sector, the implementation of the SSE would be promoted through different services, such as the so-called “Exercise Looks After you” [47]. In the private sector, it is also possible to implement the SSE in associations or centres for the care or entertainment of the elderly.

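### The analysis named for hypothesis 2 has no arm term, so if the arms are pooled, outcomes that SSE improves can look related through group membership alone

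*Protocol article*

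**What the plan says.** The Introduction states two hypotheses. The first is that "SSE will enhance regucalcin levels, executive function, physical fitness, balance, fall risk, fear of falling, and body composition in older people". The second is that "changes in executive function and regucalcin will be related to falls, body composition, and physical fitness in older people". The Discussion counts "studying the correlations of these changes with the variables of fall prevention, physical condition, and body composition" among the things that earlier SSE research has not done.

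Section 2.8 gives one sentence on method for the second hypothesis: Pearson's "bivariate correlations and linear regression will be also computed for analysing the associations between variables". It closes the intention-to-treat paragraph, whose analysis set is defined by "This analysis will consider all randomly assigned participants in their respective group". It comes directly after the sentence beginning "Alpha level shall be set at", which fixes p ≤ 0.05.

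Covariates are named for one model only: "Repeated measures ANOVA will be applied to calculate the intervention effects on the different dependent variables, adjusted by age and baseline outcomes". Nothing says whether the associations are estimated across both arms, within arms or adjusted for arm. The same procedures are repeated per protocol, where "only the volunteers who have completed more than 80% of training sessions will be considered". The control arm has no training sessions, so read literally that set holds SSE participants only.

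**The concern.** Hypothesis 1 expects SSE to shift the variables that hypothesis 2 then relates to one another. If it does, SSE participants sit higher on both variables and controls lower on both (or the reverse sign, for outcomes where improvement is a decrease). That separation between arms is itself a correlation in the pooled data. A pooled Pearson test then no longer has an expected value of zero when the two variables are unrelated within arms, and the distortion grows with the success of the intervention.

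At stake is the reading of one of the two stated hypotheses. The Discussion and Conclusions already connect better regucalcin levels with lower cancer risk, and the Discussion proposes regucalcin as an ageing biomarker. A correlation produced by shared group membership could be taken as support for such a mechanism.

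**Working it through.** The protocol gives no figure for the association analysis, so there is none to reproduce. Its sample-size section supplies the only effect size.

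**Inputs from the protocol**
- Section 2.3: 45 per arm, 20% loss, hence 45 × 0.80 = 36 completers per arm.
- Section 2.3: regucalcin difference 38.48 AU, SD 192.4, hence d = 38.48/192.4 = 0.20.
- Section 2.1: allocation 1:1. Section 2.8: alpha 0.05.

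**Assumptions**
- Two-sided testing (sidedness is not stated).
- Zero correlation within each arm, which is the null case.
- Normal data with equal variances.
- Arms pooled.
- Effects other than 0.20 SD, because the protocol gives none for executive function, fitness, falls or body composition.

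**Induced correlation.** Scale each variable to within-arm SD 1, with arm effects d1 and d2. With 1:1 allocation, each pooled variance is 1 + d²/4 and the pooled covariance is d1·d2/4. So

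r = (d1·d2/4) / √[(1 + d1²/4)(1 + d2²/4)]

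Examples:
- 0.2 and 0.8: 0.04/√(1.01 × 1.16) = 0.04/1.082 = 0.037.
- 0.8 and 0.8: 0.16/1.16 = 0.138.
- 1.0 and 1.0: 0.25/1.25 = 0.20.

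**False-positive rate** of the two-sided 5% test, by simulation (20,000 to 40,000 trials per scenario):

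| d1, d2 (SD) | Induced r | Pooled, 45 per arm | Pooled, 36 per arm |
|---|---|---|---|
| 0.2, 0.2 | 0.010 | 5% | 5% |
| 0.2, 0.8 | 0.037 | 6% | 6% |
| 0.2, 1.2 | 0.051 | 8% | 7% |
| 0.5, 0.5 | 0.059 | 8–9% | 8% |
| 0.5, 0.8 | 0.090 | 13–14% | 12% |
| 0.8, 0.8 | 0.138 | 25–26% | 21% |
| 1.0, 1.0 | 0.200 | 48–49% | 40% |

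With arm removed (partial correlation), the rate is about 5% in every row and at both sample sizes.

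**Sensitivity of the 0.20.** The SD of 192.4 is given for regucalcin, and the text does not say whether it is the SD of levels or of changes. If it is the SD of levels and the baseline to follow-up correlation were 0.8 (assumed), the SD of change would be 192.4 × √[2(1 − 0.8)] = 192.4 × 0.632, and the standardised effect 0.20/0.632 = 0.32. With a second effect of 0.8, r = 0.064/√(1.0256 × 1.16) = 0.059, the same as the 0.5 and 0.5 row.

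**The case against.** Several points on the other side have force.

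- **Pooling is inferred.** A reader might infer that the protocol prescribes a correlation over both arms. It does not say so. Membership of the intention-to-treat set makes pooling the natural reading, no more. This stands and makes the point conditional.
- **Regression is named in the same sentence.** A regression can include arm, and a full protocol or analysis plan may list covariates. That also stands. But the bivariate test is named beside it and nothing says which result decides hypothesis 2. Adding arm would replace that named test rather than fill in its detail.
- **The effect is small at the protocol's own figure.** A reader might infer that unrelated outcomes will look related. At 0.20 SD for regucalcin they mostly will not: the rate is 5% to 8%. The large rates need large effects on both variables, which the documents do not give. Equally, 0.20 SD is described as a minimum difference, and no figure bounds the pairs that involve executive function.
- **Change against change is one reading.** The hypothesis can also be read as change against level. If the level is measured after treatment starts, the same mechanism applies. If it is a baseline level, randomisation removes it.
- **A pooled correlation is a valid marginal description.** True. It does not separate the treatment effect from the association between the variables within arms, and only the latter could speak to a mechanism.

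**Conclusion.** The point holds in conditional form. Section 2.8 offers hypothesis 2 a bivariate test that cannot separate the treatment effect from the association within arms, and states no arm term for the regression. If the arms are pooled, the excess over 5% is slight for pairs that include regucalcin at 0.20 SD (5% to 8% with 45 per arm). It becomes material only when SSE moves both variables strongly, reaching about 25% at 0.8 SD on each and about 49% at 1.0 SD on each. Those larger effects are assumptions.

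The documents do not support the stronger claim that the trial is bound to report spurious associations. Pooling is unstated, an arm-adjusted regression is not excluded, and the one documented effect is small. The case for changing the text is that a method which holds the 5% level in every scenario is available at almost no cost.

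**What to change.** In section 2.8, replace the sentence on associations with a statement that hypothesis 2 is tested by regression of one change score on the other, with arm, age and the baseline values as covariates, or by a partial correlation given arm. State that the conclusion on hypothesis 2 rests on that arm-adjusted estimate. Show the correlation within each arm beside it, so that a reader can see whether the association is similar in both. Label any pooled Pearson coefficient as descriptive.

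The cost is one sentence of text and one degree of freedom for arm, with no new data.

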## 3. Discussion

Internationally, there are more than 300 publications on SSE in high-impact journals, but none have addressed the aspects that this project aims to study. There are many published studies on physical exercise in older people; however, there is no publication that studies the benefits of SSE on executive function, regucalcin, as well as studying the correlations of these changes with the variables of fall prevention, physical condition, and body composition in older people.

The implementation of the SSE has been investigated in adult populations [42,43], as well as in other populations with pathologies such as diabetes mellitus type 2 [44], Parkinson’s [45], and fibromyalgia [23], among others. Therefore, we hypothesize that a 6-month intervention based on SSE will improve the regucalcin levels, executive function, physical fitness, balance, fall risk, fear of falling, and body composition in older people over 65 years old. Furthermore, if the efficacy of this training system is demonstrated as an improvement in the regucalcin levels, it could reduce the risk of developing cancerous tissues, as well as being used as a biomarker in “active” ageing. Similarly, if there are encouraging results in cognitive performance and balance tests, it could indicate an improvement in functionality and performance in activities of daily living. These improvements will provide older people with independence from external aids that will be needed in the after-effects of ageing. Therefore, the implementation of SSE program could be applied by several agents interested in taking advantage of the benefits of this activity.

The SSE training method stands out because it requires neither expensive material nor any specific installation (it can be carried out in open and enclosed spaces) and reports a high applicability due to its adherence and feasibility [46]. Thus, it is a low-cost system standardized by different levels of difficulty (see methodology) that can be implemented at low cost in the public and private health sectors. Therefore, within the public health sector, the implementation of the SSE would be promoted through different services, such as the so-called “Exercise Looks After you” [47]. In the private sector, it is also possible to implement the SSE in associations or centres for the care or entertainment of the elderly.

This study protocol may have the following limitations: (1) difficulty recruiting individuals and having them adhere to a 24-week study plus the pre-intervention, intermediate intervention, and post-intervention assessment period; (2) the inability of some participants to complete the sessions due to COVID-19 infection; (3) there will be not follow-up phase after the end of intervention. Moreover, we recommend that future studies implement a follow-up phase at least one month after the end of the intervention. In addition, we encourage other researchers to replicate this research in adults or children to learn more about possible effects of SSE training protocols.

## 4. Conclusions

This project will investigate the effectiveness of SSE in people over 65 years of age for 6 months with the aim to analyse the effects of SSE on regucalcin, executive function, physical fitness, balance, fall risk, fear of falling, and body composition. Improvements in these variables will mean a reduced risk of developing cancerous tissues and improved performance in activities of daily living. If this intervention proves to be effective, it could be implemented in those centres, entities, and associations specialized in elderly care.

## Figures and Tables

**Figure 1 ijerph-19-03086-f001:**
[figure not shown]
Study flowchart.

**Table 1 ijerph-19-03086-t001:** Square Stepping Exercise (SSE) progression for intervention.

Month	Weeks	Frequency (Days a Week)	Session Time (min)	Difficulty (Level)
1	1–2	2	40	Beginner 1
	3–4	2	40	Beginner 2
2	5–6	2	40	Intermediate 1
	7–8	2	40	Intermediate 2
3	9–10	2	40	Intermediate 3
	11–12	2	40	Advanced 1
4	13–14	2	40	Advanced 2
	15–16	2	40	Advanced 3
5	17–18	2	40	Advanced 3
	19–20	2	40	Advanced 3
6	21–22	2	40	Advanced 3
	23–24	2	40	Advanced 3

**Table 2 ijerph-19-03086-t002:** Usual composition of an SSE session.

**Warm-up** (10 min)
Joint movement
**Main Part** (40 min)
Patch of the patterns realised in the prior session
Understanding and execution of SSE pattern 1
Understanding and execution of SSE pattern 2
Understanding and execution of SSE pattern 3
Understanding and execution of SSE pattern 4
**Cool-down** (10 min)
Stretch
Rest
Final thought

**Table 3 ijerph-19-03086-t003:** Measurements calendar for both groups.

Assessment	Baseline	Month 2	Month 4	Month 6
Sociodemographic data	**x**			
Bodyweight	x	x	x	x
Height	x	x	x	x
Regucalcin	x	x	x	x
Executive function	x	x	x	x
Physical condition	x	x	x	x
Balance	x	x	x	x
Fall risk	x	x	x	x
Fear of falling	x	x	x	x

## Data Availability

Not applicable.
